### Brain metastases at presentation

If a patient presents with 1–3 brain metastases and ablation of those metastases (with surgery or radiation) is judged to be clinically required regardless of the treatment of extracranial metastases, it is permitted. Those treated metastases count within the total number of 10 lesions. The patient would then be randomized to treatment of the extracranial disease or not.

### Patients already receiving systemic therapy

If a patient is already receiving systemic therapy, they are still eligible for enrollment. For example, if a patient with 5 metastases has been on pemetrexed for a year and is planning to continue, they can still be randomized, and if allocated to the standard arm would continue to receive pemetrexed; on the experimental arm SABR would be delivered between cycles, possibly requiring a break in systemic therapy to comply with the timing of systemic therapy described in the Systemic therapy section.

## Interventions

### Standard arm (arm 1)

Radiotherapy for patients in the standard arm should follow the principles of palliative radiotherapy, for the purpose of alleviating symptoms or preventing imminent complications. Recommended dose fractionations in this arm will include 8 Gy in 1 fractions, 20 Gy in 5 fractions, and 30 Gy in 10 fractions. Patients in Arm 1 should not receive stereotactic doses or radiotherapy boosts, unless there is a clearly known clinical benefit (e.g. stereotactic radiation to new brain metastases when all disease is controlled on systemic therapy).

Systemic therapy will be pre-specified based on the standard of care approach for that patient, and it may include systemic therapy (cytotoxic, targeted, hormonal, or immunotherapy) or observation. See Brain metastases at presentation section for the timing of systemic therapy.

### Experimental arm (arm 2)

Stereotactic radiation in Arm 2 will be delivered with three major guiding principles:
**Minimization of Toxicity**: The SABR doses used herein are lower than those used for radical treatments, and normal tissue tolerance doses will never be exceeded. Concurrent chemotherapy or targeted therapy at the time of radiotherapy is not allowed.**Minimization of Treatment Time**. To avoid delays in proceeding to systemic therapy, all SABR will be delivered over the course of 2 weeks.**Pre-planning required before enrollment:** To ensure safety, all patients require a pre-plan of their SABR treatments before enrollment. If a patient undergoes pre-planning but cannot be randomized due to failure to generate an acceptable plan, the centre will receive modest compensation to cover pre-planning costs. The baseline information of such patients will be captured (i.e. the Eligibility Checklist and Baseline Form), but they will not be followed for outcomes.

#### Dose/fractionation

Each lesion may be treated with 1, 3, or 5 fractions, depending on the local practice of the enrolling institution and treating physician. All doses are prescribed to the periphery of the planning target volume (PTV).

Acceptable fractionations are listed in Table 1. Three-fraction regimens will deliver a fraction every second day, and five-fraction regimens are delivered daily. All treatments must be completed within 2 weeks (10 working days) in order to avoid delays in starting systemic therapy.

**Table 1 Tab1:** Allowable doses and fractionations*

Number of Fractions	Preferred Dose	Acceptable Doses	Major Deviation
1	20 Gy	16–24 Gy	< 16 Gy or > 24 Gy
3	30 Gy	24–33 Gy	< 24 Gy or > 33 Gy
5	35 Gy	25–40 Gy	< 25 Gy or > 40 Gy

*Note that centres should use doses that standard at their institutions based on the specific clinical situation, within these guidelines. For example, if the standard dose for a 2.5 cm brain metastasis is 24 Gy in 3 fractions, which is an ‘acceptable dose’, that should be used instead of the ‘preferred dose’

#### Immobilization

Immobilization will be as in the original SABR-COMET trial protocol [11, 12].

#### Imaging/localization/registration

Patients will undergo planning CT simulation with axial CT images obtained throughout the region of interest. For centres using stereotactic radiosurgery platforms, real-time tumor tracking and orthogonal imaging systems are permitted.

Patients treated at the VUmc in Amsterdam may be treated with MRI-guided delivery if deemed appropriate by the treating oncologist, using daily plan adaption as has been described previously [16–19]. The "4D-CT procedures" section will not apply to these patients.

#### 4D-CT procedures

4-dimensional CT will be used for tumors in the lungs, liver, or adrenals. 4D-CT quality assurance procedures are as per the previous SABR-COMET trial [11, 12].

#### Volume definitions (arm 2)

For all lesions, the gross tumor volume (GTV) will be defined as the visible tumor on CT and/or MRI imaging +/− PET. No additional margin will be added for microscopic spread of disease (i.e. Clinical Target Volume [CTV] = GTV). For vertebral body lesions, although some centres consider the entire vertebral body as the CTV, that is not preferred in this trial due to the risk of large cumulative amounts of bone marrow being irradiated. It is strongly preferred that vertebral PTV volumes consist of the GTV (as defined on CT and MRI) with a small margin for motion, and NOT include the whole uninvolved vertebral body. A Planning Target Volume (PTV) margin of 2–5 mm will be added depending on site of disease, immobilization, and institutional set-up accuracy: 2 mm margins should be used for spinal stereotactic treatments, 0–2 mm for brain tumors, and 5 mm for other sites.

Targets should be named based on the organ involved, and numbered cranially to caudally for each organ. For example, in a patient with 1 brain and 3 lung lesions, nomenclature would be: GTV_brain_1, GTV_lung_1, GTV_lung_2, and GTV_lung_3, and corresponding PTV_brain_1, PTV_lung_1, PTV_lung_2_, and PTV_lung_3, representing the lesions from superior to inferior.

For spinal lesions, a pre-treatment MRI is required to assess the extent of disease and position of the cord. This must be fused with the planning CT scan. A Planning Organ at Risk Volume (PRV) expansion of 2 mm will be added to the spinal cord, and dose constraints for the spinal cord apply to this PRV. Alternatively, the thecal sac may be used as the PRV. For radiosurgery platforms, a PRV margin of 1 mm is permitted for the spinal cord.

#### Organ at risk (OAR) doses

OAR doses are listed in Additional file 1. OAR doses may not be exceeded. In cases where the PTV coverage cannot be achieved without exceeding OAR doses, the PTV coverage is to be compromised. All OARs within 5 cm of the PTV must be contoured. This should be tested for each PTV by creating a 5 cm expansion to examine which OARs lie within that expansion.

#### Treatment planning

Treatment can be delivered using static beams (either 3D-conformal radiotherapy or intensity-modulated) or rotational therapy (volumetric modulated arc therapy, or tomotherapy). Priority will be placed on generating clinically acceptable plans while minimizing complexity, planning time, and treatment time.

##### Dose constraints may not be exceeded

If a dose constraint cannot be achieved due to overlap of the target with an organ at risk, the dose can be reduced, the number of fractions can be increased, or the target coverage compromised in order to meet the constraint. The decision as to whether to reduce the dose to the whole target, or part of the target (i.e. by compromising the PTV coverage), is left to the discretion of the treating physician. In cases where the target coverage must be reduced, the priority for dose coverage is the GTV (e.g. attempt to cover as much of the GTV as possible with the prescription dose). For vertebral tumors, note that the spinal cord constraints apply to the PRV (see the "Volume definitions (arm 2)" section).

For all targets, doses should be prescribed to 60–90% isodose line surrounding the PTV, and all hotspots should fall within the GTV. 95% of the PTV should be covered by the prescription dose, and 99% of the PTV should be covered by 90% of the prescription dose.

Doses must be corrected for tissue inhomogeneities. Several non-overlapping 6/10 MV beams (on the order of 7–11 beams) or 1–2 VMAT arcs combined possibly with a few non-coplanar beams should be utilized. Non-coplanar beams can be used to reduce 50% isodose volume.

The number of isocentres is at the discretion of the treating physician, physicists, and dosimetrists. Generally, metastases can be treated with separate isocenters if they are well-separated.

The scheduling and sequence of treating each metastasis is at the discretion of individual physicians, but in general should begin with the brain, due to risks associated with progression. All SABR must be completed within 2 weeks.

#### Quality assurance (arm 2)

In order to ensure patient safety and effective treatment delivery, a robust quality assurance protocol is incorporated. The following requirements must be completed for each patient:
Prior to treatment, plans for each patient must be peer-reviewed, either by discussion at quality assurance (QA) rounds or by another individual radiation oncologist.All radiotherapy plans must meet target dose levels for organs at risk (Additional file 1). Prior to plan approval, the dose to each organ at risk must be verified by the physicist or treating physician.All dose delivery for intensity-modulated plans (including arc-based treatments) will be confirmed before treatment by physics staff.

#### Systemic therapy

Patients treated with prior systemic therapy are eligible for this study, however, systemic therapy agents that are cytotoxic, immunotherapeutic, or molecularly targeted agents are NOT allowed within the period of time commencing 2 weeks prior to radiation lasting until 1 week after the last fraction. Hormone therapy is exempted from this and is allowed during treatment. Use of chemotherapy schemes containing potent enhancers of radiation damage (e.g. gemcitabine, doxorubicin) are discouraged within the first month after radiation.

#### Concurrent steroid treatment for brain metastases

Patients who require systemic steroids as treatment for brain metastases or related edema should be tapered as quickly and as safely possible. Prolonged use of steroids should be avoided, and steroid use will be recorded.

#### Further radiotherapy for progressive disease at new metastatic sites

Patients in Arm 1 who develop new, untreated metastatic deposits should be treated with standard-of-care approaches. SABR to those sites is not permitted, except for unique scenarios where it would be considered standard of care (e.g. all disease controlled on systemic therapy with a newly developed brain metastasis).

Patients in Arm 2 who develop new, untreated metastatic deposits should be considered for SABR at those sites, as appropriate, if such deposits can be treated safely with SABR, and if the treating institution offers SABR for that body site. If SABR is not possible, then palliative RT can be delivered if indicated. Patients in Arm 2 who develop progression at lesion previously treated with SABR may be considered for palliative radiation or repeat SABR if safe and dose constraints can be met.

#### Quality assurance for centres joining study

Prior to opening the study, each participating research centre will be required to send to one of the Principal Investigators a mock treatment plan for the anatomic sites that will be treated (e.g. lung, brain, liver, adrenal), to ensure that the treatment plans are designed in compliance with the protocol. The principal investigators will provide pertinent CT datasets. Alternatively, a pre-plan for a patient enrolled on this trial may be used for credentialing. Each participating research centre can choose which tumor sites will be treated at their individual centre (i.e. some centres may only choose to treat a subset of the eligible metastatic sites). Sites that have prior accreditation for SABR through a clinical trial (e.g. SABR-COMET, or organ-specific SABR trials) are exempt from this requirement for the organ sites that have been accredited in those trials.

## Subject discontinuation / withdrawal

Subjects may voluntarily discontinue participation in the study at any time. If a subject is removed from the study, the clinical and laboratory evaluations that would have been performed at the end of the study should be obtained. If a subject is removed because of an adverse event, they should remain under medical observation as long as deemed appropriate by the treating physician.

## Follow-up evaluation and assessment of efficacy

### Follow-up Prior to Progression

Patients will be seen every 3 months post-randomization for the first 2 years, and every 6 months until 5 years after treatment (Table 2). At each visit, a history and physical examination will be conducted by the oncologist, and CTC-AE toxicities recorded. The FACT-G and EQ-5D-5 L quality of life questionnaire is to be completed at each visit.

**Table 2 Tab2:** Follow-up Evaluations

Test and Procedures	1–4 weeks post SABR treatment and prior to systemic therapy	3 Months post Randomization	Years 1–2	Years 3–5	First progression or study completion (at 5 years post-randomization) whichever is first
			Every 3 months	Every 6 months	
History and Physical including assessment of side affects			X	X	
CT or MR head, CT chest, abdomen, pelvis			X	X	
Bone Scan			X	X	
Completion of questionnaires (FACT-G and EQ-5D-5 L)			X	X	
Blood Samples for Correlative Studies (i.e studies that are associated with the main study)	X (Arm 2)	X (Arm 1 & 2)			X (Arm 1 & 2)

CT head (or MR head), CT chest, abdomen and pelvis, and bone scans will be repeated every 3 months for the first 2 years, then every 6 months until 5 years have elapsed. Head imaging can be omitted for histologies without a propensity for brain metastases (e.g. prostate), and bone scans may be omitted in patients without bone metastases at presentation. PET scanning may be used in follow-up for patients who were staged with a PET scan for trial entry. In such cases, the PET replaces the CTs of the chest, abdomen, pelvis and the bone scan; brain imaging would still be required for histologies with a propensity for brain metastases.

Since many patients will be receiving systemic therapy and separately-timed imaging may be required to assess response to systemic therapy, attempts should be made to avoid duplication of scans. The imaging requirements herein may be adjusted by ±4 weeks in order to align with scans used to assess response to systemic therapy.

### Follow-up after progression

After progression, patients randomized to Arm 2 will be considered for salvage SABR if new sites of disease develop, as long as it can be delivered safely, and to a maximum of 10 lesions total (including lesions treated at baseline).

After progression, for patients in either arm, additional visits, imaging or laboratory investigations should be carried out at the discretion of the oncologist. Additional treatment (e.g. further systemic therapy) is at the discretion of the treating oncologists. However, additional treatments, toxicities of study treatment, vital status and quality of life should still be collected, along with any further anti-cancer treatment delivered (e.g. further palliative radiation or systemic therapy), and this may be ascertained remotely (e.g. by phone or mail) to minimize visit burden for patients.

### Assessment of efficacy

Overall Survival
◦ Defined as time from randomization to death from any causeProgression-free survival
◦ Defined as time from randomization to disease progression at any site or death.◦ Progression is defined as per the Response Evaluation Criteria in Solid Tumors (RECIST) 1.1 guidelines (http://recist.eortc.org/recist-1-1-2/). It can be difficult to distinguish recurrence from fibrosis/pseudoprogression after stereotactic radiation in some locations, such as the lung or brain. In such cases, if the RECIST 1.1 criteria for progression are met, the situation should be counted as progression unless there is imaging follow-up with stability of the imaging findings for at least 6 months.◦ As per RECIST 1.1, when findings of progression are equivocal (e.g. small new lesions of uncertain etiology), the patient should still be followed. If progression is confirmed at the next assessment, the date of progression assigned is the earlier date when progression was first suspected.Time to development of new metastatic lesions
◦ Defined as the time from randomization to the development of new lesions that were not detectable at the time of randomization. In a situation where indeterminate lesions were present at randomization, progression at one of those lesions does not count as a new metastatic lesion.◦ As noted above, as per RECIST 1.1, when findings of new metastases are equivocal (e.g. small new lesions of uncertain etiology), the patient should still be followed. If progression is confirmed at the next assessment, the date of progression assigned is the earlier date when progression was first suspected.Quality of life
◦ Assessed with the Functional Assessment of Cancer Therapy: General (FACT-G) and the EQ-5D-5 LToxicity
◦ Assessed by the National Cancer Institute Common Toxicity Criteria (NCI-CTC) version 4 for each organ treated (e.g. liver, lung, bone)]

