#### Previously treated metastases

Patients with prior metastases that have been treated with ablative therapies (e.g. SABR, surgery, radiofrequency ablation) are eligible, as long as those metastases are controlled on imaging. In that case, the previously treated lesions are counted toward the total of 10 (e.g. a patient with 3 previous brain metastases treated is allowed to have up to 7 other metastases for enrollment).

If a patient has received systemic therapy and the number of metastases has been reduced, they are eligible for enrollment as long as the total number of metastases prior to systemic therapy was 10 or fewer.

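### The pseudoprogression exemption does not require unchanged treatment during the 6 stable months, which leaves secondary PFS open to bias toward SABR

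*Protocol article*

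**What the plan says.** The article defines PFS from randomization to progression at any site or death, with progression by RECIST 1.1 (Assessment of efficacy). It then makes one exception: "It can be difficult to distinguish recurrence from fibrosis/pseudoprogression after stereotactic radiation in some locations, such as the lung or brain". A finding of that kind that meets the RECIST criteria "should be counted as progression unless there is imaging follow-up with stability of the imaging findings for at least 6 months".

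Three other parts of the article bear on how this works:

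- **Treatment after progression.** Follow-up after progression states: "Additional treatment (e.g. further systemic therapy) is at the discretion of the treating oncologists". The section on further radiotherapy for progressive disease allows palliative radiation or repeat SABR to a lesion in Arm 2 that progresses after SABR.
- **Imaging after progression.** The same follow-up section says "additional visits, imaging or laboratory investigations should be carried out at the discretion of the oncologist".
- **Who has stereotactically treated lesions.** Arm 2 receives SABR to all known disease. For the standard arm, "Patients in Arm 1 should not receive stereotactic doses or radiotherapy boosts, unless there is a clearly known clinical benefit". Arm 1 lesions can still qualify in limited ways: "Patients with prior metastases that have been treated with ablative therapies (e.g. SABR, surgery, radiofrequency ablation) are eligible", and patients with 1–3 brain metastases may enter where "ablation of those metastases (with surgery or radiation) is judged to be clinically required".

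PFS is a secondary endpoint, compared by stratified log-rank test (Analysis plan). It is also one of two limbs of the futility rule, which stops the trial only if the hazard ratios for OS and PFS both exceed 1.0 (Interim analysis).

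**The concern.** Six months of stability is meant to show that the finding was never a recurrence. It shows that only if nothing else explains the stability. If the lesion was re-irradiated, or the patient was moved to a new drug, stability may only show that salvage worked. Read literally, the rule then deletes a genuine PFS event.

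The deletion is asymmetric. A lesion in Arm 1 that grows, prompts a change of therapy and then stabilises normally remains an event, because it was not treated stereotactically. The same course at a SABR-treated lesion in Arm 2 can be reversed.

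Reversal also needs at least 6 months of later imaging. If an uncertain finding counts as progression by default, it is unclear whether the patient stays on scheduled scans or moves to scans at local discretion. In the second case, whether an event can be reversed depends partly on local practice.

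At stake are the secondary PFS comparison and the PFS limb of the futility rule.

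**Working it through.** **Step 1. The text.** The exemption has three conditions: the finding follows stereotactic radiation, it is hard to distinguish from fibrosis or pseudoprogression, and later imaging is stable for at least 6 months. None concerns treatment in those months. The sections on further radiotherapy and on follow-up after progression permit local re-treatment and new systemic therapy. So a salvaged true recurrence can satisfy the rule as written.

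**Step 2. The plan's own figures.** The article gives no number for PFS, for pseudoprogression or for use of the exemption. Its design inputs reproduce. With exponential OS, medians of 10 and 17 months, accrual R = 60 and follow-up F = 12, P(event) = 1 − (e^(−λF) − e^(−λ(R+F)))/(λR), which is 0.897 in Arm 1 and 0.771 in Arm 2. The 1:2 average is 0.813. Then 122/0.813 gives 151, and 151/0.95 gives 159, as stated. This confirms the accrual frame used below; the point does not depend on it.

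**Step 3. Size if true progressions are wrongly erased.**

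- From the document: 53 v 106 patients (159 at 1:2), accrual over 60 months plus 12 months of follow-up.
- Assumption: exponential PFS with median 6 months in both arms, so the true HR is 1. The 6 months is the Arm 1 median quoted from the earlier SABR-COMET trial.
- Assumption: an erased event is replaced by one 6 months plus an exponential time (median 6 months) later, and only where 6 months of follow-up remain.
- Assumption: a quarter of Arm 2 first events are eligible findings. Deaths, new lesions and progression at lesions not treated stereotactically cannot be reversed.
- Assumption: 5%, 10% or 20% of eligible findings are true recurrences wrongly erased. As a share of all Arm 2 first events that is 0.25 × 5% = 1.25%, 0.25 × 10% = 2.5% and 0.25 × 20% = 5%.

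| Share of all Arm 2 first events erased | HR, very large cohort (Cox) | HR, trial-sized simulation (log-rank score) | Chance of a significant PFS result for SABR |
|---|---|---|---|
| 0% | 1.00 | 0.99 | 3% |
| 1.25% | 0.98 | 0.97 | 4% |
| 2.5% | 0.96 | 0.95 | 5% |
| 5% | 0.92 | 0.91 | 7% |

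The trial-sized estimate sits about 0.01 below the large-cohort value, even with nothing erased.

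**Step 4. The opposite error.** Suppose the exemption did not exist and 5%, 10% or 20% of Arm 2 patients (assumption) had pseudoprogression meeting RECIST at 3–9 months. With no true effect, the large-cohort HR becomes about 1.03, 1.05 or 1.11, against SABR. Steps 3 and 4 pull in opposite directions, and the document gives neither fraction.

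**Step 5. The interim look.** It takes place once the 75th patient has been followed for 6 months. Scans are every 3 months, so a finding at the first scan cannot show 6 months of stability until about month 9. Recent uncertain findings therefore still count as progression at the interim, which works against SABR there.

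**The case against.** The strongest defence is that the exemption is needed and narrow. Pseudoprogression after SABR arises almost only in Arm 2, so counting every RECIST finding would penalise SABR (step 4). The rule covers only uncertain findings, with "after stereotactic radiation in some locations, such as the lung or brain" as its setting. Its default is progression, and new lesions, progression elsewhere and deaths always count. Missing scans leave the event in place, which does not favour SABR. All of this stands.

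A reader might infer that PFS is therefore biased toward SABR, or that the rule always works in SABR's favour. The documents do not support that. Only wrongly erased true recurrences favour SABR, the net direction depends on two unreported fractions, and the interim effect runs the other way. Nor is Arm 1 wholly outside the rule. A reader might also apply an erasure rate of 10% or 20% to every Arm 2 event and reach an HR near 0.86 or 0.73. That would include deaths and new metastases, which the rule cannot touch.

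It can be argued that a patient whose finding is unresolved has not yet progressed and so stays on scheduled imaging, and that a lesion sent for re-treatment has been judged recurrent and is no longer uncertain. Both readings are sensible, but the text states neither.

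Finally, an article condenses a fuller protocol, and a sensitivity analysis may well sit elsewhere. That is fair for the sensitivity analysis. The endpoint rule, however, is set out here with its conditions, and the condition that makes stability interpretable is not among them.

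**Conclusion.** The point holds in limited form. As written, the rule can remove a true, successfully salvaged recurrence from PFS, mainly in Arm 2. That leaves secondary PFS and the PFS limb of the futility rule open to bias toward SABR. Neither net direction nor size can be determined from the document.

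On the assumptions in step 3, the HR under no true effect moves to about 0.97–0.91, and the chance of a false significant result for SABR rises from about 3% to about 4–7%. The quarter share and the 5–20% range are assumptions without a source in the article. The primary endpoint and the sample size are unaffected, and futility stopping also needs an OS hazard ratio above 1.0. The change is worth making because it is cheap and strengthens an otherwise sound rule.

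**What to change.** 1. **Keep the exemption and add one condition, for counting PFS events only.** Reversal is allowed only if no new systemic therapy (beyond that pre-specified for the patient) and no local treatment to that lesion began between the apparent progression and the end of the 6-month stable period. Otherwise the original progression date stands. This does not restrict what treatment patients receive.

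2. **Add a PFS sensitivity analysis with no reversal in either arm**, stating that it is biased against SABR. Do not substitute it in the interim futility rule. With 75 patients accrued evenly at 159/60 per month, a true PFS HR of 0.80, an Arm 1 median of 6 months and pseudoprogression at 3–9 months (assumptions), the chance that the PFS HR exceeds 1.0 is about 20% without pseudoprogression. If it occurs in 10% or 20% of Arm 2 patients and is all counted, the chance rises to just under 30% or just under 40%.

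3. **Reconcile Follow-up after progression with Assessment of efficacy.** State that patients with a possible pseudoprogression stay on the imaging schedule in Follow-up Prior to Progression until the finding is resolved.

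The cost is a few sentences and one extra analysis. Further anti-cancer treatment is already to be recorded after progression, though start dates and treated lesion must be captured. The downside is that a few genuine pseudoprogressions in patients whose therapy changed will count as events.
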